### Intervention

In the percutaneous EVAR or TEVAR group, access is obtained through puncture of the common femoral artery deployment of two ProGlide devices (Abbott Vascular, Santa Clara, Calif) using a Preclose technique. The technique consists of deploying the needles of the first ProGlide device 30° medially or laterally from the midline. The second ProGlide needles are then deployed vertically from the first device, and then 16Fr sheath is inserted in the percutaneous access in EVAR and 18Fr sheath is used in TEVAR. When endovascular aortic repair is finished, the pretied knot and sutures of both devices are tightened and form knots by using the closure device remotely to achieve hemostasis. Pressuring and bandaging the puncture site gently also help stop bleeding. After percutaneous closure, it is necessary to observe whether the distal artery pulse well.

In the cutdown EVAR or TEVAR group, a 5-cm longitudinal incision is positioned in the groin area and common femoral artery is controlled by vessel loops. Femoral access is obtained through puncture under direct vision. After endovascular repair, the femoral artery is repaired thoroughly by a running 6-0 prolene suture. The subcutaneous tissue and skin are then sutured in standard fashion layer by layer.

### Assignment of intervention

Cohort EVAR and TEVAR in the SWEET trial are designed as a parallel randomized controlled, single-blind, single-center non-inferiority trial in a 1:1 ratio. The flow diagram for the study is outlined in Figure 1. After eligibility screening, eligible subjects in the two cohorts will be randomly allocated to either intervention groups receiving percutaneous access endovascular aortic repair or control groups receiving cutdown access endovascular aortic repair separately. As for patients who require brachial artery access in Cohort TEVAR, the assignment will be based on their femoral artery access, independent of the approach for upper extremity access.

**Figure 1 F1:**
[figure not shown]
Flow of participants randomly assigned to percutaneous groups and cutdown groups.

Block randomization stratified by age and body mass index (BMI) using permuted blocks of random sizes will be performed with 1:1 allocation in both cohorts. Randomization sequence is generated by SPSS 26.0 statistical software by a biostatistician. The block size will be concealed until the primary endpoints are analyzed. An independent research coordinator will be responsible for keeping the sequentially numbered allocation sequence list, and will inform the surgeons about the assigned access procedure prior to intervention. To avoid performance bias, every surgeon must have had 10 or more ProGlide procedures, and experience of at least 20 surgical cutdowns to expose the access artery is also needed.

Obviously, trial participants and operating team cannot be blinded to the allocation. The data will be entered into the computer in separate tables by employees outside the research team so that the analysts can analyze data without knowing the allocation information. Therefore, only data analysts are blinded in this study.

### Outcome measures

The endpoints or composites in the SWEET trial are classified as ClinROs and PCOs. Cohort EVAR and TEVAR share the same primary and secondary endpoints. Primary and secondary outcomes will be assessed at 2 weeks, 1 month, and 3 months after surgery. An overview of the clinical outcome measures based on the SPIRIT recommendations is provided in Table 1.

**Table 1 T1:** SPIRIT schedule for the SWEET randomized controlled trial.

	**Pre-study**		**Study visit**	**Follow-up**		
	**Enrollment**	**Baseline/** **Allocation**	**Treatment**	**2-week** **after surgery**	**1-month after surgery**	**3-month after surgery**
**Timepoint**	**-T1**	**0**	**T1**	**T2**	**T4**	**T5**
Enrollment						
Eligibility screen	**×**					
Informed consent	**×**					
Clinical interviews		**×**				
Allocation		**×**				
Interventions			**×**			
Assessments						
*Primary ClinRO endpoint*						
Access-related complications			**×**	**×**	**×**	
Access site infection			**×**	**×**	**×**	
Bleeding/ hematoma			**×**	**×**	**×**	
Access-related arterial injury			**×**	**×**	**×**	
Femoral artery occlusion			**×**	**×**	**×**	
Pseudoaneurysm			**×**	**×**	**×**	
Lymphorrhagia/seroma			**×**	**×**	**×**	
Access-related nerve injury			**×**	**×**	**×**	
Wound dehiscence			**×**	**×**	**×**	
*Primary PCO endpoint*						
Time back to normal life/work				**×**	**×**	**×**
*Secondary ClinRO endpoints*						
Operative time			**×**			
Length of hospital stay			**×**	**×**	**×**	
30-day limb graft occlusion			**×**	**×**	**×**	
30-day overall complications			**×**	**×**	**×**	
30-day mortality			**×**	**×**	**×**	
*Secondary PCO endpoints*						
Quality of life scores				**×**	**×**	
Duration of access-related pain				**×**	**×**	**×**

#### Primary outcomes

The primary ClinRO endpoint is access-related complications assessed in-hospital, 2 weeks and 1 month after surgery. The definition of access-related complications includes

Access-site infection: inflammation of the groin presenting redness, swelling or exudation and requiring consecutive oral or intravenous antibiotics therapy.Bleeding/hematoma: fresh oozing blood or old blood stains seen on wound dressing/blood accumulation around the access site.Access-related arterial injury: arterial injuries requiring endarterectomy or patching due to the access technique.Femoral artery occlusion: femoral artery thrombosis presenting as distal artery pulse poorly requiring thrombectomy.Pseudoaneurysm: false aneurysm at the site of arterial injury presenting as a painful and pulsatile mass.Lymphorrhagia/seroma: swelling at access site caused by damage to lymphatic duct during access obtaining.Access-related nerve injury: nerve injuries presenting as persistent paresthesia of the thigh due to the access technique.Wound dehiscence: a partial or complete separation of previously close access wound edges.

The primary PCO endpoint is time (days) back to normal life/work assessed at 2 weeks by telephone interview and checked at 1 month and 3 months in outpatient clinics after surgery. To determine the outcomes that patients care most, we conducted a preliminary survey in 50 patients who received EVAR or TEVAR prior to our trial, and recovery time back to normal life or work represented the major PCO endpoint.

#### Secondary outcomes

The secondary ClinRO endpoints will be assessed in-hospital, 2 weeks and 1 month postoperatively, involving

Operative time (minutes): defined as duration of whole EVAR or TEVAR procedure.Length of hospital stay (days): defined as the period of time a patient remains in hospital.30-day limb graft occlusion: defined as a complete limb occlusion regardless of symptoms or lumen stenosis of more than 50% detected by image examination within 30 days postoperatively (17).30-day overall complications: defined as all systemic or local complications within 30 days postoperatively, whether related to the access or not.30-day mortality: defined as all-cause deaths occurring in the intervention population within 30 days postoperatively.

The secondary PCO endpoints involve quality of life scores and duration of access-related pain, which will be assessed simultaneously with the primary PCO endpoint.

Quality of life scores: participants' perception of physical and mental health form various aspects over time, scored with European Quality of Life 5 Dimensions (EQ-5D) questionnaire.Duration of access-related pain (days): length of participants' unpleasant sensory and emotional experience associated with access wound.

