### Data collection and management

#### Data collection methods

Baseline data required are shown in Supplementary Table S5 (Supplementary Material). Age, sex, BMI, comorbidity etc., should be collected before assignment to achieve maximum balance between groups. Anatomical characteristics of aortic aneurysm, aortic dissection and access artery that have potential impact on treatment success and prognosis should also be routinely measured by the operating team with computed tomography angiography (CTA). In particular, the heavily calcified femoral artery, defined as an estimated over 50% area of calcification in the superficial surface, needs more attention of investigator (7). So does the severe tortuous iliac artery, which is defined as any portion of iliac artery with tortuous angle more than 90° so that visually doubled or more on a single slice of axial CTA (18).

All patients after surgery will be examined for access-related complications during the everyday ward rounds and dressing changes. After discharge, the remaining primary and secondary outcomes can be gotten by telephone interviews and outpatient re-examination over several months. Quality of life scores will be quantified by EQ-5D questionnaire during follow-up, which reduces the variability in life quality assessment by various researchers. The EQ-5D questionnaire evaluates overall quality of life from 5 dimensions of mobility, self-care, usual activities, pain/discomfort, anxiety/depression, with each dimension ranging level 1 to 5. And its reliability and validity have been verified in many studies (19, 20).

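### Recovery time and access-pain duration are counted in days but first asked about at 2 weeks, so their dates rest on recall by unblinded patients; a dated card and an in-hospital pain field would reduce that error cheaply

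*Protocol article*

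**What the plan says.** The Primary outcomes section sets the unit: "The primary PCO endpoint is time (days) back to normal life/work". The same sentence sets the collection: "assessed at 2 weeks by telephone interview and checked at 1 month and 3 months in outpatient clinics after surgery". The Secondary outcomes section also defines access-related pain by its length in days, and ties the secondary patient-centered outcomes to the same contacts, as ones "which will be assessed simultaneously with the primary PCO endpoint".

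Table 1 agrees for these two endpoints. Each row is marked at 2 weeks, 1 month and 3 months and is blank in the Treatment (T1) column. Every access-complication row is marked at T1.

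In-hospital assessment is written for the clinician-reported side: "The secondary ClinRO endpoints will be assessed in-hospital, 2 weeks and 1 month postoperatively". Under Data collection methods, patients are "examined for access-related complications during the everyday ward rounds and dressing changes". The outcomes left over are described as obtained after discharge, by telephone or in clinic.

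Under Assignment of intervention, participants and operators are unblinded and only the analysts are blinded. Continuous endpoints are to be compared by a generalized linear model. The sample size rests on access-site complications, not on any patient-centered outcome.

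**The concern.** The contacts are far more widely spaced than the unit of the endpoint. A patient whose groin pain stops, or who resumes normal life, in the first two weeks is first asked for the date at the 2-week call. Someone who recovers soon after the 1-month visit is asked about two months later. In both cases the number that enters the model is a remembered date.

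Two kinds of error can follow. Random misdating, including rounding to whole weeks, adds variance. Differential misdating, for instance if patients expect to recover sooner after a puncture than after a 5-cm incision, goes directly into the estimated difference. Neither blinded analysts nor covariate adjustment can take it out.

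This matters because the article's rationale is that the choice of access may matter more for patient experience than for procedural success, and because neither endpoint was powered. Dates not recorded at the time cannot be recovered later.

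**Working it through.** The plan states no sample size, power, SD or target difference for either endpoint, so it has no figure of its own to reproduce. The check compares the schedule with the unit of measurement.

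**Inputs**
- Unit: days, for both endpoints (Primary outcomes; Secondary outcomes).
- Contacts: 2 weeks, 1 month, 3 months (Primary outcomes; Table 1). Assumption: 1 month = 30 days, 3 months = 90 days.
- In-hospital mark at T1: none for either endpoint (Table 1).
- Blinding: analysts only (Assignment of intervention).

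**Look-back windows**
- Surgery to 2-week call: 14 − 0 = 14 days.
- 2 weeks to 1 month: 30 − 14 = 16 days.
- 1 to 3 months: 90 − 30 = 60 days.

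The longest window is the last, so the problem is not confined to early recovery.

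**What the later checks add.** Suppose pain ends on day 3. The 2-week call asks about a date 14 − 3 = 11 days back, the 1-month visit about one 30 − 3 = 27 days back, and the 3-month visit about one 90 − 3 = 87 days back. A check can expose an inconsistent answer. It cannot supply a fresher one, and it is again self-report.

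**Where daily ward contact helps.** The groin is seen every day in hospital, so pain that ends before discharge could be dated as it happens. Return to normal life or work will mostly come after discharge, and ward rounds cannot date it. The article gives no expected length of stay, so the share of pain durations that would benefit is unknown.

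**Illustration only.** If nothing but the interval were known and the event were uniform within it, the error SD would be gap/√12: 14/√12 = 4.0, 16/√12 = 4.6 and 60/√12 = 17.3 days. Adding a 4-day error SD to an assumed between-patient SD gives a variance ratio of 1 + 4²/SD²:
- SD 5 days: 1 + 16/25 = 1.64
- SD 10 days: 1 + 16/100 = 1.16
- SD 15 days: 1 + 16/225 = 1.07

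The error SD and all three between-patient SDs are assumptions.

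**The case against.** The article does not contradict itself on these two endpoints: text and table agree. Asking patients at follow-up when they got back to normal is an ordinary way to collect such an outcome. That stands. The point is an improvement in measurement, not the correction of an error.

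The full protocol or its forms might contain a diary. That is possible, and the absence of one from a journal article is no finding. However, the printed schedule is explicit, and it places the first enquiry about both endpoints at 2 weeks.

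A blank at T1 may mean only that a duration is entered once it has ended. That is reasonable, but it leaves pain that ends on the ward without a planned contemporaneous record.

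A reader might infer that the primary outcome loses a known amount of precision, between 7% and 64% in variance. The documents do not support this. The plan asks for a day, not an interval, and the 4-day error matches a patient who remembers nothing within the first two weeks. A range that wide, built on assumed SDs, shows the mechanism and not its size.

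A reader might also infer that early dates hang on a single telephone call, or that daily ward contact could repair the primary patient-centered outcome. The 2-week answer is rechecked twice, and the ward argument reaches pain duration only.

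Finally, a card is completed by the same unblinded patient, so expectation can still move the marked day. That also stands.

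**Conclusion.** The point holds as a limited measurement weakness. Under the printed schedule, both day-count endpoints depend on retrospective self-report by patients who know their allocation, over windows of up to about 14, 16 and 60 days. The window lengths rest only on the 30- and 90-day reading of the visits.

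Neither the size nor the direction of any effect can be derived from the documents, and no change in power or sample size can be calculated. It would be wrong to conclude that the recovery-time comparison is invalid or biased towards percutaneous access. Recall error can be reduced cheaply. Expectation bias cannot be removed from an unblinded self-report, and the article openly says that participants cannot be blinded. The change is worth making because one of the two endpoints is primary and the cost is low.

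**What to change.** 1. In Table 1, mark duration of access-related pain at T1, and add one yes/no field for access-site pain to the form used at the daily ward round. This helps pain duration only.
2. At discharge, give every patient in both arms the same one-page dated card or message form, on which to mark the first day free of access-site pain and the first day back to normal life/work.
3. At the planned 2-week, 1-month and 3-month contacts, take the dates from the card where there is one. Record for each date whether it came from the card or from recall, and pre-specify a sensitivity analysis by source.
4. State in the article or report that this limits recall error and rounding to whole weeks, and that expectation effects remain.

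The cost is a card, one ward field and one source field. No visit is added, and the endpoint definitions and analysis model are unchanged. The downsides are a small burden on patients and some cards lost, left blank or filled in late; the source field identifies dates that fall back on recall but cannot by itself detect a back-filled card.

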#### Withdraw and dropout

Patients who agreed to participate in the trial can quit the study at any time for any reason without any consequences. After withdrawal, the subjects will not be replaced by others and their randomization number will not be re-used. Subjects are considered as dropout if they are lost to follow-up within 1-month postoperatively or they withdraw from the study.

### Data collection and management

#### Data collection methods

Baseline data required are shown in Supplementary Table S5 (Supplementary Material). Age, sex, BMI, comorbidity etc., should be collected before assignment to achieve maximum balance between groups. Anatomical characteristics of aortic aneurysm, aortic dissection and access artery that have potential impact on treatment success and prognosis should also be routinely measured by the operating team with computed tomography angiography (CTA). In particular, the heavily calcified femoral artery, defined as an estimated over 50% area of calcification in the superficial surface, needs more attention of investigator (7). So does the severe tortuous iliac artery, which is defined as any portion of iliac artery with tortuous angle more than 90° so that visually doubled or more on a single slice of axial CTA (18).

All patients after surgery will be examined for access-related complications during the everyday ward rounds and dressing changes. After discharge, the remaining primary and secondary outcomes can be gotten by telephone interviews and outpatient re-examination over several months. Quality of life scores will be quantified by EQ-5D questionnaire during follow-up, which reduces the variability in life quality assessment by various researchers. The EQ-5D questionnaire evaluates overall quality of life from 5 dimensions of mobility, self-care, usual activities, pain/discomfort, anxiety/depression, with each dimension ranging level 1 to 5. And its reliability and validity have been verified in many studies (19, 20).

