#### Analysis of primary and secondary outcomes

Generalized linear model (GLM) will be used to compare continuous primary and secondary endpoints, and further adjustment for age, gender, BMI and femoral artery calcification will be performed by multivariate GLM analysis. Logistic regression using generalized estimating equations (GEE) will be applied to compare categorical primary and secondary endpoints. Using multivariate GEE models, the subsequent analysis will be adjusted for age, gender, BMI and femoral artery calcification. The access-related complications are counted and analyzed by the number of femoral accesses instead of the number of patients.

To address heterogeneity among study population, pre-specified subgroup analyses will be performed in the following populations: heavily calcified femoral artery vs. lightly calcified femoral artery, tortuous iliac artery vs. non-tortuous iliac artery, obesity or overweight vs. normal weight, smoking vs. none, elderly or octogenarian vs. younger population.

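### EQ-5D is scheduled only after surgery in the visible protocol and its baseline is not among the stated covariates, so this secondary comparison gives up precision that a short questionnaire could supply

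*Protocol article*

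**What the plan says.** Three places in the protocol article time the EQ-5D, and all are after surgery.

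- Data collection methods: "Quality of life scores will be quantified by EQ-5D questionnaire during follow-up".
- Secondary outcomes: quality of life and pain duration are endpoints "which will be assessed simultaneously with the primary PCO endpoint". Under Primary outcomes that endpoint is "assessed at 2 weeks by telephone interview and checked at 1 month and 3 months in outpatient clinics after surgery".
- Outcome measures, Table 1: the row "Quality of life scores" is marked at 2 weeks and 1 month. It has no mark at enrollment, baseline/allocation or 3 months.

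For continuous endpoints, Analysis of primary and secondary outcomes says that "further adjustment for age, gender, BMI and femoral artery calcification will be performed by multivariate GLM analysis". Randomization is stratified by age and BMI.

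On baseline data, Data collection methods says: "Age, sex, BMI, comorbidity etc., should be collected before assignment to achieve maximum balance between groups". It also names CTA anatomy and refers to Supplementary Table S5 for the full list. That table is not shown.

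**The concern.** Patients come to endovascular repair with differing health, and part of that difference will still be present in their scores some weeks later. If the pre-operative score is not measured or not modelled, that part stays in the error term. The cohorts are small and are reported separately: Sample size gives 54 evaluable patients per group in Cohort EVAR and 45 in Cohort TEVAR. A chance difference in pre-operative quality of life is quite possible at those sizes, and the planned covariates can remove only the part they share with it.

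Quality of life matters to this trial even as a secondary endpoint, because the Introduction and Discussion give the lack of patient-centered data as a main reason for doing it. A pre-operative score that was never taken cannot be recovered by a later analysis plan, so the time to settle this is while patients are still being enrolled.

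**Working it through.** **Inputs from the protocol.** Evaluable patients per group are 54 (EVAR) and 45 (TEVAR), with 1:1 allocation. No sample size, power or standard deviation is given for EQ-5D, so there is no EQ-5D figure to reproduce.

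The group sizes themselves do reproduce from n = (z_α + z_β)² × [p₁(1 − p₁) + p₂(1 − p₂)] / (distance to margin)², with z_α = 1.645 and z_β = 0.842:

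- EVAR: 6.183 × 0.1747 / (0.10 + 0.0417)² = 53.8, so 54; 54/0.9 = 60.
- TEVAR: 6.183 × 0.1572 / (0.15 − 0.002)² = 44.4, so 45; 45/0.9 = 50.

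This match uses a one-sided 5% level. The stated bilateral 5% would give 69 and 57. That is a separate matter; 54 and 45 are used here only as the planned sizes.

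**Assumption.** The correlation ρ between baseline and follow-up EQ-5D is not in the documents, so a range of 0.3 to 0.7 is used.

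**Step 1: gain against no adjustment.** Adjusting for baseline multiplies the variance of the treatment difference by 1 − ρ² and the standard error by √(1 − ρ²). The detectable difference at 80% power and two-sided 5% is (1.960 + 0.842) × √(1 − ρ²) × √(2/n), in SD units.

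| ρ | Variance ratio | SE cut | Detectable, EVAR (n = 54) | Detectable, TEVAR (n = 45) |
|---|---|---|---|---|
| none | 1.00 | – | 0.54 SD | 0.59 SD |
| 0.3 | 0.91 | 5% | 0.51 SD | 0.56 SD |
| 0.5 | 0.75 | 13% | 0.47 SD | 0.51 SD |
| 0.7 | 0.51 | 29% | 0.39 SD | 0.42 SD |

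Equivalently, 54 patients per group would act like 54/0.91 = 59 to 54/0.51 = 106.

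**Step 2: gain against the planned model.** The plan already adjusts for four covariates, so Step 1 is not the right comparison for the adjusted analysis. Suppose the four explain 10% of the variance, and 25% is explained once baseline EQ-5D is added (ρ = 0.5, with the covariates' 10% lying inside what baseline explains). The residual variance ratio is (1 − 0.25)/(1 − 0.10) = 0.83, and √0.83 = 0.91, a cut of about 9% rather than 13%. With less overlap between the covariates and baseline EQ-5D the cut would be larger.

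**Step 3: chance imbalance.** The standard error of the difference in baseline means is √(2/n): 0.19 SD for EVAR and 0.21 SD for TEVAR. An imbalance beyond 0.2 SD in either direction then has probability of about 30% (EVAR) or 34% (TEVAR). It would shift the follow-up difference by ρ × 0.2: 0.06, 0.10 or 0.14 SD for ρ of 0.3, 0.5 or 0.7. These figures ignore stratification and covariates, which remove the part linked to age, BMI, gender and calcification.

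**Step 4: visits.** The text ties EQ-5D to visits at 2 weeks, 1 month and 3 months. Table 1 marks it at 2 weeks and 1 month only. The two statements conflict.

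**The case against.** Four objections carry weight.

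- **The baseline list is unseen.** A reader might infer that no pre-operative EQ-5D is taken and that change from before surgery cannot be reported. The documents do not support that as fact. The in-text list of baseline items is open-ended, Supplementary Table S5 is not shown, and Table 1 has no row for any baseline variable, not even age or BMI. Its empty cell is therefore weak evidence. What stands is that every visible statement of EQ-5D timing is postoperative.
- **The covariate set is generic.** One list serves all continuous endpoints, and an endpoint-specific baseline term could be left to an analysis plan. That is fair for the model, but not for the measurement: no analysis plan can supply a score that was not collected.
- **Randomization already protects the comparison.** A reader might infer that the quality-of-life result would be biased or invalid. It would not be. Allocation is random and stratified by age and BMI, the estimate is unbiased on average, and chance imbalance is already reflected in its standard error. Only precision and correction of a realised imbalance are lost.
- **The gain is assumed.** No correlation is stated, and the larger figures compare with no adjustment at all. Both are true, which is why a range and the smaller figure from Step 2 are given.

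**Conclusion.** This is a low-cost improvement to a secondary endpoint; it does not invalidate any analysis. The visible protocol places EQ-5D after surgery only and leaves its baseline out of the stated covariates. Under an assumed correlation of 0.3 to 0.7, it forgoes a standard-error reduction of about 5% to 29% against no adjustment. Against the planned four-covariate model the loss is smaller: about 9% at a correlation of 0.5, if those covariates explain 10% of the variance and all of that is shared with baseline EQ-5D. The group sizes and both primary endpoints are unaffected.

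The scheduling part depends on Supplementary Table S5: if EQ-5D is listed there, only the covariate part remains. The conflict between Table 1 and the text on the 3-month assessment stands either way.

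**What to change.** 1. Check Supplementary Table S5. If EQ-5D is absent, add it there; in either case mark it in Table 1 under baseline/allocation. Complete it before allocation, because participants are not blinded and knowing the assigned access could colour their answers.
2. In the EQ-5D model, add baseline EQ-5D to age, gender, BMI and femoral artery calcification. Keep all four; nothing here gives a reason to drop any.
3. Reconcile Table 1 with Secondary outcomes on whether EQ-5D is assessed at 3 months.

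The cost is a few minutes per patient. A clinical interview is already scheduled at baseline, and a research nurse already meets each patient before the procedure. The change of model falls under what Protocol amendments lists as potentially major, so it would need notification. Patients already enrolled would lack the baseline value. The existing rule of multiple imputation for missing baseline covariates would cover them, but imputed values recover little of the lost information, so the gain shrinks as the number already enrolled grows.
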